### Recruitment of participants

This study will apply purposive sampling for the recruitment of participants. Participants will be included if they:
Are diagnosed with symptomatic knee OA as defined by the American College of Rheumatology’s Clinical Criteria for Classification and Reporting of knee OA [22–24]Are diagnosed with Grade I and II knee OA based on the Kellgren-Lawrence severity scale [25]Are femaleAge 50 and olderHave body mass index (BMI) between 18.5 and 29.9 kg/m^2^Have knee pain ≥ two on a VAS

Participants with the following conditions will be excluded:
Electrical devices implantNeurological disorders (i.e., stroke)Wheelchair boundSignificant cognitive impairmentPresent systemic inflammatory arthritis (i.e., gout)History of hip or knee arthroplastyHistory of trauma or surgical arthroscopy of either knee in the last 6 monthsReceived knee intra-articular injection within the last 3 monthsUnder anticoagulant therapy, recent or imminent surgery (within 3 months)Involved in any study related to exercise program within the last 6 months

In addition, eligible participants will be considered as drop-outs if they request to withdraw due to any reasons or if they are unable to complete 75% of the intervention program.

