**Fig. 4 Fig4:**
[figure not shown]
Closed kinetic chain exercise program

1) Terminal end knee extension in standing (maximum 15° of knee flexion) [31];

2) Wall slide (semi squat);

3) Forward step up and down;

4) Side step up and down;

For both OKC and CKC groups, participants will perform all exercises for ten repetitions three times a week, for 8 weeks. Following that, if they consistently obtain less than three on the VAS scale [32], they are encouraged to increase the intensity of the exercise by increasing the number of sets with the same repetitions for each exercise.

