### Primary outcomes

#### Pain

Pain intensity will be assessed using the (VAS) [32]. It is a reliable, valid, and responsive tool, and frequently used as an outcome measure for pain [32]. It consists of a bidirectional 10 cm straight line, where 0 cm is “no pain,” and 10 cm is “worst imaginable pain,” located at either end of the line [32]. Participants will be asked to choose a number that best represents their pain level. The VAS scoring will be recorded at the baseline assessment, after every exercise session throughout the 8-week intervention, and lastly at the end of the intervention program.

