### Additional measures

#### Adverse event

As a co-intervention, daily oral nonsteroidal anti-inflammatory drugs (NSAIDs) in the form of PCM 3000 mg [24, 44, 45] are provided. However, the usage of the PCM is not compulsory. Participants can consume the PCM as per their needs and record the usage in the diary provided. The pain scale (VAS) will also be recorded in the diary during the intervention period for all three groups of participants. Any adverse event during the intervention will be recorded in the provided diary. The participants will also be reminded to inform the physiotherapist immediately if they faced any problem during the eight weeks of the exercise program. The contact number is stated on the consent form. If necessary, the physiotherapist will contact the medical supervisor and co-supervisors for further investigation or management.

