### Statistical analysis

Data will be entered and analyzed using SPSS version 25 (IBM Corp., Armonk, NY, USA). Only the data from the participants who have completed at least 75% of the study intervention will be analyzed. Data from drop outs will not be included in the analysis. Descriptive data will be reported as a mean ± standard deviation. Two-way ANOVA will be used to test the within- and across- group comparison of the VAS, WOMAC, and OAKHQOL scores, and isokinetic knee muscle strength, as well as lower limb biomechanics during gait and STS. The level of significance is set at a *p*-value < 0.05. A least significant difference (LSD) post hoc test will be conducted following any significant differences from the two-way ANOVA test.

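### The completers-only rule is worded for all data, so any by-arm summary of diary pain or adverse events made under it would leave out those who stopped because exercise hurt

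*Protocol article*

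**What the plan says.** All references are to the protocol article.

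- **Statistical analysis** sets the rule in two sentences: "Only the data from the participants who have completed at least 75% of the study intervention will be analyzed" and "Data from drop outs will not be included in the analysis". The tested outcomes come afterwards: "Two-way ANOVA will be used to test the within- and across- group comparison of the VAS, WOMAC, and OAKHQOL scores", then isokinetic strength and gait and sit-to-stand biomechanics. Nothing ties the exclusion to that list or to particular time points.
- **Recruitment of participants** treats as drop-outs those who ask to "withdraw due to any reasons or if they are unable to complete 75% of the intervention program". Pain on exercise is not excepted.
- **Pain** (under Primary outcomes) has VAS recorded at baseline, at the end, and "after every exercise session throughout the 8-week intervention".
- **Adverse event** (under Additional measures) states: "The pain scale (VAS) will also be recorded in the diary during the intervention period for all three groups of participants". It continues: "Any adverse event during the intervention will be recorded in the provided diary".
- **The closed kinetic chain (CKC) exercise program**, in the text on progression for both exercise groups, encourages participants to increase intensity "if they consistently obtain less than three on the VAS scale".
- **Monitoring** makes the researcher responsible for tracking drop-out reasons and listing all adverse events for reports. It does not limit this to completers and does not mention diary VAS.

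**The concern.** A completers-only set is a choice about which participants enter the outcome comparison. Here it is worded as a rule for data in general, and the diary holds data of another kind. A VAS reading taken after a home session shows how that session was tolerated, as well as being a measurement of a primary outcome. The protocol uses it this way when it makes low VAS the condition for progression, and it mentions diary VAS alongside adverse-event recording.

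A participant who finds the programme too painful and stops is a drop-out by definition. If diary pain or adverse events are summarised by arm under the stated rule, the summary covers only those who carried on. It is then selected on the quantity being described. If one programme causes more pain-related stopping than the other, its remaining diaries will look better than the experience of those who started it. The Discussion section expects the results to guide the design of home programmes. In my judgement, someone choosing between open and closed chain exercise would also want to know how often each hurt enough to make people stop.

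**Working it through.** **1. Who is removed.** The drop-out definition has two limbs: a request to withdraw for any reason, and failure to complete 75%. A participant who stops early because of pain meets at least one. One who eases off after reaching 75%, without asking to withdraw, stays in.

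**2. Which readings are removed.** The exercises are prescribed three times a week for 8 weeks: 3 × 8 = 24 sessions. The threshold is 0.75 × 24 = 18 sessions. An exerciser who falls short on the 75% limb can therefore have completed up to 17 sessions, leaving up to 17 post-session VAS readings outside the analysis.

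**3. How many people, at the planned drop-out.** The Sample size calculation section gives 18 needed per group, 20% drop-out, and 22 recruited per group (66 in total).
- Plan's own figure: 18 × 1.2 = 21.6, rounded up to 22. (Dividing instead gives 18 / 0.8 = 22.5, that is 23; the difference does not affect this point.)
- Left out per arm: 22 − 18 = 4, or 4/22 = 18.2%. Directly, 0.20 × 22 = 4.4.
- Two exercise arms: 2 × 4 = 8 of 44. All three arms: 3 × 4 = 12 of 66.

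**4. How many of those stopped because of pain.** The 20% covers every cause and the document gives no split. The range is 0 to 4 per arm, or 0 to 8 across the two exercise arms.

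**5. What this could do to a diary mean.** Take a week in which all 22 in an arm still have readings. Let *k* be the number who later stop because of pain, and suppose their mean VAS is *g* points above everyone else's. The mean over all 22 is then higher than the completers' mean by *k* × *g* / 22. For *k* from 0 to 4 this is 0 to 0.18 × *g*. The document gives neither *k* nor *g*, so no figure in VAS points can be derived.

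**6. What is kept elsewhere.**

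| Information on a participant who stops because of pain | Statistical analysis | Monitoring |
|---|---|---|
| Adverse events | Not named; excluded if analysed under the rule | All listed |
| Reason for stopping | Not named | Recorded |
| Diary VAS before stopping | Excluded | Not mentioned |

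No section brings drop-outs' diary VAS back into a summary.

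**The case against.** The strongest reply is that no analysis is described in which this harm would occur. The document sets out neither a by-arm adverse-event summary nor a tolerability analysis of diary VAS. The exclusion rule stands directly before the two-way ANOVA and can naturally be read as the analysis set for that test. The reader's main need, how many stopped because of pain, can be met from the drop-out reasons kept under Monitoring. The Adherence section adds contact three times a week that also tracks adverse effects. A by-arm safety table is commonly left to an analysis plan or full protocol that is not shown here.

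Much of this stands. The point is conditional on someone summarising these data under the stated rule, and it does not rest on the absence of a named harm analysis. What remains is that the rule itself is in the document and is unrestricted. Read literally, it would govern any such summary and would be out of line with the Monitoring section.

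Two stronger readings are tempting and should be resisted. A reader might infer that the plan discards safety data. It does not: events and reasons are collected and listed for everyone. A reader might also infer that confining the rule to the efficacy and biomechanical outcomes would rescue the diary VAS. It would not, because VAS is itself a primary outcome and one of the variables named for the ANOVA. The limit has to be by assessment time point, with diary readings kept explicitly.

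**Conclusion.** The point holds in a limited form. As written, the completers-only rule covers all data, and those who stop because exercise hurts are drop-outs. Any by-arm description of post-session VAS or adverse events made under it would therefore omit the participants who tolerated the programme worst. At the planned drop-out that is about 4 of 22 per arm, of whom 0 to 4 may have stopped because of pain.

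This assumes that the rule is read literally, that drop-out runs at the planned rate, and that diary or adverse-event data are summarised by arm at all. The direction of any distortion between the open and closed chain arms depends on whether pain-related stopping differs between them, which the document cannot tell us. Because the Monitoring listing keeps events and reasons, importance is minor. Whether a completers-only set suits the pre/post efficacy comparison is a separate question and is not judged here.

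**What to change.** In the Statistical analysis section:

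1. State that the completers-only rule applies, at most, to the pre- and post-intervention assessments entered in the two-way ANOVA.
2. Add wording such as: *Adverse events and withdrawals because of pain will be summarised descriptively by arm in all randomised participants. Available diary VAS up to the point of stopping will be described by week for the two exercise arms; control-arm diary VAS will be shown separately, as it is not recorded after exercise.*

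This brings the analysis text into line with the Monitoring section. It needs no new endpoint, hypothesis test, visit or participant: only a few sentences and one descriptive table. Recruitment was still open at publication, and the Monitoring section gives the ethics-committee route for modifications.

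The costs are entering drop-outs' diaries, a possibly less favourable tolerability figure, and two limits on interpretation. The document does not say that drop-outs return their diaries, so some may be missing. Those who stop early also contribute fewer sessions, which is why the description should be by week, with the number contributing shown, and not a single average.

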**Method:**

A total of 66 individuals with painful early knee OA, aged 50 years and above, with body mass index (BMI) between 18.9kg/m^2^ and 29.9 kg/m^2^ in Kelantan, Malaysia, will be recruited in this study. Participants will be randomly allocated into three different groups, either the OKC, CKC, or control groups. All three groups will attend an individual session with a physiotherapist. The participants in the OKC and CKC groups will perform the exercises three times weekly for 8 weeks at their home. The control group will receive education about clinical manifestations, risk factors, diagnosis, treatment, and nursing care for knee via printed materials. The primary outcomes include self-reported pain scores (visual analog scale), disability scores (Western Ontario and McMaster Universities Arthritis Index), and quality of life scores (Osteoarthritis Knee and Hip Quality of Life). Secondary outcomes include lower limb biomechanics during gait and sit-to-stand as well as isokinetic knee strength. The outcomes will be measured before and after the intervention.

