### Sample size calculation

The sample size was determined using G*Power statistical software version 3.1.9.2 (Universität Düsseldorf, Germany) based on the primary outcome variables of pain and function based on the visual analog scale (VAS) scores as well as the Western Ontario and McMaster Universities Arthritis (WOMAC) Index respectively. The sample size for this study was determined to detect an effect size of 0.5, based on a previous study [21] with an alpha value of 0.05. Eighteen participants per group will be sufficient to achieve a statistical power of 0.8. By anticipating a dropout rate of 20%, a total of 22 participants per group (total *N* = 66) will be recruited.

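### The two-way ANOVA of before/after scores names no deciding term, leaves out the baseline adjustment and lets any significant term open the LSD comparisons; a baseline-adjusted ANCOVA as the single deciding test would settle all three

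*Protocol article*

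**What the plan says.** The Statistical analysis section gives one test for all primary and secondary outcomes: "Two-way ANOVA will be used to test the within- and across- group comparison of the VAS, WOMAC, and OAKHQOL scores", and likewise for isokinetic strength and the gait and sit-to-stand variables. The threshold is common to all: "The level of significance is set at a *p*-value < 0.05". The follow-up step is: "A least significant difference (LSD) post hoc test will be conducted following any significant differences from the two-way ANOVA test".

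The Abstract (Method) gives the time structure: "The outcomes will be measured before and after the intervention". The second factor is therefore evidently time, measured on the same participants. Pain is also recorded between these two visits: "The VAS scoring will be recorded at the baseline assessment, after every exercise session throughout the 8-week intervention". The Statistical analysis section does not say whether those interim scores enter the ANOVA.

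The section does not say which ANOVA term answers the between-group question, and it mentions no adjustment for baseline. The Sample size calculation section rests on 18 evaluable participants per group: "Eighteen participants per group will be sufficient to achieve a statistical power of 0.8".

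**The concern.** The primary aim in the Background is a between-group comparison of the exercise programmes, with a hypothesis about change relative to usual care. A two-way ANOVA of group by time has three terms, and they answer different questions.

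- **Group main effect:** compares group means averaged over baseline and week 8. Randomised groups have the same expected baseline, so this average shows only half of any week-8 difference.
- **Time main effect:** shows change common to all groups and says nothing about treatment.
- **Group-by-time interaction:** compares change between groups. With two time points it is the same test as a one-way ANOVA of change scores.

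Only the interaction is aimed at the trial's question, and the text does not single it out. With three groups, LSD comparisons keep the within-outcome familywise error at 5% only if one 5% omnibus test guards them. A rule under which any significant term opens them removes that protection. It also leaves the deciding term open to choice once the results are seen. In a trial of 18 evaluable participants per arm, the precision lost by not adjusting for baseline also matters.

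**Working it through.** **Inputs from the protocol article.** Three randomised groups; 18 evaluable per group, so N = 54; two assessments on the same people; significance level 0.05; effect size 0.5 ("The sample size for this study was determined to detect an effect size of 0.5, based on a previous study [21] with an alpha value").

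**Assumptions.** The pre/post correlation r is not given; I use 0.3, 0.5 and 0.7. Scores are normal with SD 1 at both times and equal expected baselines. The metric of 0.5 is not stated; I read it as Cohen's f for the week-8 means, with both exercise arms equally better than control. For means 0, δ, δ, f = δ√(2/9) = 0.471δ, so f = 0.5 gives δ = 1.06 SD.

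**The plan's own figure.** A one-way ANOVA with f = 0.5 and three groups reaches power 0.80 with 14 per group; 18 per group gives 0.90. The stated pairing of 18 per group with power 0.8 is therefore not reproduced under this reading. That is a separate matter; I take 18 per group as given.

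**1. Literal two-way ANOVA (pre and post treated as independent).** The variance of a participant's mean score is (1+r)/2, where the test assumes 1/2. The variance of a change score is 2(1−r), where the test assumes 2. So under no effect the group F is inflated by about 1+r and the interaction F is shrunk by about 1−r. With critical value F(2, 102) = 3.085, the rejection rates are roughly exp(−3.085/(1+r)) and exp(−3.085/(1−r)):

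| r | Group term, formula | Group term, simulated | Interaction, formula | Interaction, simulated |
|---|---|---|---|---|
| 0.3 | 0.093 | 0.10 | 0.012 | 0.014-0.016 |
| 0.5 | 0.128 | 0.13-0.14 | 0.002 | 0.003 |
| 0.7 | 0.163 | 0.17 | <0.001 | <0.001 |

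The nominal rate is 0.05. Simulations here and below used 40,000 to 60,000 trials per setting.

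**2. Mixed ANOVA, more than one term allowed to open the post hoc step.** Each term alone holds 5%. The group term depends on each participant's sum of scores and the interaction on the difference. With equal variances these are independent, so the chance that at least one is significant under no group effect is 1 − 0.95² = 0.0975. Simulation gives 0.097-0.098.

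**3. Power with 18 per arm.** For the week-8 scores alone the noncentrality is Nf² = 54 × 0.25 = 13.5. Then:

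- Mixed group main effect: difference halved (f²/4), variance (1+r)/2, so λ = 13.5/[2(1+r)], df 2 and 51.
- Mixed interaction: variance 2(1−r), so λ = 13.5/[2(1−r)], df 2 and 51.
- ANCOVA: residual variance 1−r², so λ = 13.5/(1−r²), df 2 and 50.

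| r | λ group / interaction / ANCOVA | Group main effect | Interaction | ANCOVA |
|---|---|---|---|---|
| 0.3 | 5.19 / 9.64 / 14.84 | 0.49 | 0.77 | 0.92 |
| 0.5 | 4.50 / 13.50 / 18.00 | 0.44 | 0.90 | 0.96 |
| 0.7 | 3.97 / 22.50 / 26.47 | 0.39 | 0.99 | 0.995 |

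The ANCOVA powers are simulated. The noncentral F formula gives 0.927, 0.966 and 0.996 before the small loss from chance baseline imbalance. ANCOVA's simulated type I error is 0.05 throughout.

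The residual variance of ANCOVA relative to change scores is (1−r²)/[2(1−r)] = (1+r)/2, that is 0.65, 0.75 and 0.85 at the three correlations.

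**4. If 0.5 is a standardised mean difference instead** (both exercise arms 0.5 SD better), the interaction against ANCOVA gives 0.23 against 0.33, 0.31 against 0.39, and 0.48 against 0.54. The ordering is the same; the level of power is then a sample size problem.

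**The case against.** The strongest reply is that a within-group factor crossed with an across-group factor is the ordinary description of a mixed group-by-time ANOVA. A condensed article may leave the repeated-measures detail to the full protocol or analysis plan. On that reading the interaction respects the pairing and holds 5%, and ANCOVA is a gain in precision, not a repair of validity. At correlation 0.7 the gain is negligible. All of this stands.

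Three stronger readings are therefore not supported.

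- A reader might infer that two-way ANOVA is simply the wrong test here. One of its terms is valid, so that is too strong.
- A reader might infer that before and after scores will be analysed as independent. The article does not say so, and the 10-17% error rates apply only if that is done.
- A reader might infer that LSD will compare group means averaged over time, or that a time effect alone would open the group comparisons. The wording permits both but states neither.

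The reply does not remove the rest. The article itself fixes the trigger for the post hoc tests, and fixes it as any significant result, without naming the term that decides. The 10% figure arises even in a correctly specified mixed ANOVA.

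**Conclusion.** The concern holds as a fault in how the test is fixed. Under the likely mixed reading the valid term exists but is not selected. The group main effect has power of only 0.39-0.49 in the scenario examined, because it halves the week-8 difference. Letting either the group term or the interaction open the LSD step roughly doubles the chance of a false opening, to about 10% per outcome. Under the literal reading the group term would reject 10-17% under no effect and the interaction far less than 5%.

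Against the valid interaction, ANCOVA gains 15 percentage points of power at correlation 0.3, 6 at 0.5 and under 1 at 0.7. These sizes rest on the assumed correlation, on equal variances at both visits, and on reading 0.5 as f. The halving and the 1 − 0.95² result do not depend on the correlation or on the effect size.

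**What to change.** Replace the test and the post hoc trigger in the Statistical analysis section. Suggested content: for each outcome, the week-8 score is analysed by ANCOVA with group (three levels) and that outcome's baseline score as covariate. The 2-df group test is the deciding test. Only if it is significant at 0.05 are the three baseline-adjusted pairwise differences tested by LSD. All three differences are reported with 95% confidence intervals. For pain, the week-8 assessment is the endpoint, and scores recorded after sessions are descriptive.

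Within-group changes can stay as descriptive or supportive results, since the hypotheses mention improvement after 8 weeks; they should not decide the between-group question. If the sponsor prefers to keep a mixed ANOVA, the minimum change is to call it that, and to name the group-by-time interaction as the only term that decides and the only one that opens comparisons, which should then be of change scores.

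The cost is analysis wording. Baseline values are already collected and SPSS fits the model. The Trial status section describes recruitment as ongoing, and the Monitoring section provides for modifications through the ethics committee, so the change can be recorded before the group comparison is run. It does not address the completers-only analysis set, the several primary outcomes or the sample size, which need separate attention.

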To date, open kinetic chain (OKC) and closed kinetic chain (CKC) exercises have been prescribed for knee OA patients. During OKC exercise, the distal segment of the body parts is not fixed, and it can move freely. Knee extension in the sitting position and straight leg raising (SLR) in the lying position are examples of OKC exercises. On the other hand, during CKC exercise, the distal segment of body parts remains stationary on the ground. Examples of CKC exercises include squat and leg press exercises. Both types of exercises were comparable in terms of their impact on improving pain scale, functional scores, and strength [16]. Moreover, 12 weeks of OKC, CKC, and its combination were found to significantly increase the static and dynamic quadriceps strength and thigh muscle bulk in a study that involved 96 patients with knee OA [17]. However, there is a lack of published studies that evaluate the impact of OKC and CKC on the lower limb biomechanics during gait and STS.

Exercise intervention for OA is usually conducted in the hospital or clinic under the supervision of physiotherapists. However, some patients might face logistics constraints in attending the exercise sessions [18]. To improve the adherence to exercise program, the sessions can be relocated from the hospital to other settings such as at home and in the community [7]. Apart from that, patient education is vital to improve the patients’ understanding of their current condition and to ensure compliance to exercise program and long-term self-management at home [12].

The primary aim of this randomized controlled trial (RCT) is to compare the effects of home-based OKC and CKC exercise intervention programs on pain (visual analog scale), disability scores (Western Ontario and McMaster Universities Arthritis Index), and quality of life scores (Osteoarthritis Knee and Hip Quality of Life) among patients with mild knee OA. Our secondary aim is to compare the effects of OKC and CKC exercises on lower limb biomechanics during walking gait and STS tasks. It is hypothesized that OKC and CKC exercises will result in a significant reduction of pain as well as improved functions and quality of life after 8 weeks of intervention. We also hypothesize a small but clinically relevant change in their biomechanical variables following OKC and CKC intervention. These changes may be significant when compared to the usual care group.

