### Secondary outcomes

#### Lower limb biomechanics during gait and STS

To capture the biomechanical variable, infrared cameras with three-dimensional (3D) motion capture and analysis system will be used. Kinetic data will be collected using the force platform (Bertec, Ohio, USA) to measure the ground reaction force and joint moments whereas the kinematic data will be collected by the infrared cameras at 100Hz using the Qualisys track manager software (Qualisys, Sweden) and V3D software (version 5, C-Motion, Gothenburg, Sweden). Both the kinematic and kinetic data of the lower limb will be analyzed during the gait and STS test [39]. STS is commonly used to assess the strength and balance of the lower extremities [39]. STS has been shown to have a great intra and inter-rater reliability (ICC, 0.89) among hip and knee OA patients [40].

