#### Isokinetic knee strength

Isokinetic knee flexion/extension strength will be evaluated using Biodex Dynamometer (Biodex Medical System, Shirley, NY, USA). The data to be collected will include the peak torque and muscular power of the hamstring and quadriceps. The dynamometer and chair will be adjusted to the appropriate height and length of each participant. Then, belts will be strapped on the participants to stabilize their trunk, pelvis, and contralateral thigh. The quantification of knee flexion/extension strength will be performed at the angular velocity of 180°/s [41, 42]. The speed has been chosen because it is associated with a reduction in the friction between knee cartilage, knee irritation, and other symptoms during muscle strength measurement [41]. To complete the measurement, all participants will perform each test in flexion/extension motion as hard as they can for five repetitions per set and two sets for both legs [41, 43].

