## Discussion

The prevention of knee OA is different for each individual depending on their risk factors [46]. Targeted individualized prevention techniques to ensure maximum adherence to the exercise program should be planned for each patient [46]. To achieve this, it is crucial to involved knee OA patients in the exercise program to understand their treatment preferences and improve their conditions. Apart from statistically significant differences between patient and control groups, other clinically significant differences can also be important when interpreting the trial results [47, 48]. A decrease of 2 points in the pain score and a decrease of 9.1 scores in the function subscale of the WOMAC questionnaire are examples of clinically relevant improvement [47, 49, 50]. A mere 5% change in KAM was shown to improve OA symptoms [51, 52] which will be considered as a clinically relevant improvement of the KAM in this trial. The results from this trial will provide vital evidence on clinical and biomechanical outcomes following OKC and CKC exercise programs in people with mild knee OA. Additionally, this study will help in the formulation of effective home-based exercise protocols, especially for patients with mild knee OA.

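### Every strength, gait and sit-to-stand variable is tested at p < 0.05, and no named variable decides the biomechanical hypothesis

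*Protocol article*

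**What the plan says.** The Statistical analysis section puts the three primary scores and all secondary domains through one method: "Two-way ANOVA will be used to test the within- and across- group comparison". It then gives one significance level for everything: "and isokinetic knee muscle strength, as well as lower limb biomechanics during gait and STS. The level of significance is set at a" p-value below 0.05. An LSD post hoc test follows any significant ANOVA. No secondary variable is ranked, adjusted for or called exploratory.

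The secondary domains are described as follows.

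- **Biomechanics** (Lower limb biomechanics during gait and STS): "Both the kinematic and kinetic data of the lower limb will be analyzed during the gait and STS test". The variables are neither listed nor counted.
- **Strength** (Isokinetic knee strength): "The data to be collected will include the peak torque and muscular power of the hamstring and quadriceps". Both legs are tested, at one angular velocity.

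The Background makes biomechanics in walking and STS the secondary aim and attaches a hypothesis: "We also hypothesize a small but clinically relevant change in their biomechanical variables following OKC and CKC intervention". It adds that these changes may be significant against usual care. The Discussion gives one biomechanical variable, KAM, a relevance threshold: a 5% change. The analysis section gives KAM no priority.

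**The concern.** A hypothesis about unspecified biomechanical variables, tested variable by variable at 0.05, has no defined way to succeed or fail. Any significant joint, plane, curve feature or task could be reported as support, and nothing in the plan would count against that. Strength sits outside the hypothesis, but its several scores share the same rule.

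The Discussion expects a good deal from these data: "The results from this trial will provide vital evidence on clinical and biomechanical outcomes following OKC and CKC exercise programs". If exercise type had no effect, the plan could still yield a reportable difference between arms, and readers could not tell it from chance. The three primary scores are a separate matter and are not part of this point.

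**Working it through.** **Inputs**

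- Significance level: the sample size was set "with an alpha value of 0.05", and the analysis uses the same level for each test.
- Evaluable participants: 18 per arm in three arms (Sample size calculation).
- Strength scores: 2 measures (peak torque, power) × 2 muscle groups = 4 per leg. If each leg is analysed separately, 4 × 2 = 8. Separate analysis is an assumption; the article says only that both legs are tested.
- Biomechanical variables: count not stated. As an illustration, 3 joints × 3 planes × (angle, moment) × 2 tasks = 36.
- Correlation between variables: not stated, so a range of 0 to 0.8 is shown.

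**The plan's own figure.** For one variable, the false-positive chance should be 0.05. Simulation of one variable returns 4.7–5.0%, as it should.

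**Independent tests.** The chance of at least one false positive among m tests is 1 − 0.95^m.

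- m = 4: 1 − 0.95^4 = 18.5%
- m = 8: 1 − 0.95^8 = 33.7%
- m = 13: 48.7%
- m = 14: 51.2%, the first value above one half

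**Correlated tests.** Change scores were simulated for three arms of 18 with equal correlation between variables and no true effect. Each variable had a one-way F test on change, which is the group-by-time test in a pre/post design. The table gives the chance of at least one p < 0.05.

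| Variables | corr. 0 | 0.3 | 0.5 | 0.7 | 0.8 |
|---|---|---|---|---|---|
| 4 | 20% | 18% | 16% | 13% | 12% |
| 8 | 34–35% | 30% | 26% | 19–20% | 17% |
| 14 | 51–53% | 44% | 36–37% | 26% | 21% |
| 28 | 77% | 64–66% | 49–51% | 35% | 27% |
| 36 (assumed) | 84% | 72% | 57% | 38% | 29% |

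Ranges within a cell are repeat runs and show the simulation error. At correlation 0.5 the one-half mark falls at about 28–30 variables. At 0.7 it needs 80 or more (49% at 80, 54% at 100).

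**Expected count.** Whatever the correlation, the expected number of false positives is 0.05 × m: 0.4 for 8 scores and 1.8 for 36.

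**LSD.** With three arms, LSD run only after a significant matching F test keeps the error within one outcome at 0.05. The inflation comes from the number of outcomes, not from LSD.

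**Within-group tests.** The article also plans within-group comparisons. Counting two tests for each of 8 scores gives 1 − 0.95^16 = 56.0% under independence. The conclusion does not use this figure, because a change over time within arms is not evidence of a difference between them.

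**The case against.** The best defence is that these outcomes are already labelled secondary. On this view a condensed article may leave the variable list, the ranking and any multiplicity rule to a full protocol or SAP, and adjustment across declared secondaries is a matter of judgement. Part of this stands: the missing list is not itself a fault, and the primary conclusions are untouched. But the article does not leave the rule open. It names the secondary domains and fixes the same level and post hoc test for them as for the primaries, and it states a hypothesis with no variable attached.

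Three stronger readings are tempting, and the documents do not support them.

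- **A reader might infer that a false secondary claim is more likely than not.** That needs a large family with low to moderate correlation. The article gives neither the count nor the correlation, and the strength scores alone do not reach one half on the between-arm tests.
- **A reader might infer that any significant strength score would confirm the secondary hypothesis.** The secondary aim and hypothesis in the Background cover biomechanics only.
- **A reader might infer that statistical significance alone is the stated criterion.** The hypothesis speaks of clinically relevant change, and the Discussion sets 5% for KAM. That tempers interpretation, but only KAM has such a threshold, and the analysis section makes no use of it.

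**Conclusion.** The point holds in limited form and is worth fixing before analysis. One unadjusted 0.05 covers all secondary variables, and the biomechanical hypothesis has no deciding variable. The false-positive chance is about 17–35% for eight strength scores, or 12–19% if only four are analysed. For biomechanics it cannot be stated from the article: the assumed 36 variables give 29–84%.

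These figures assume the global null, 18 evaluable participants per arm, equal correlation of 0 to 0.8, and one group-by-time test per variable. The inflation is present under every setting examined with more than one variable; its size in biomechanics is conditional.

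**What to change.** In the sections on lower limb biomechanics and Statistical analysis:

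1. Name peak KAM during gait as the key secondary outcome that decides the biomechanical hypothesis, since KAM is the only biomechanical variable with a relevance threshold. Test it at 0.05 by the group-by-time test. Use OKC versus CKC and each exercise arm versus control as follow-up contrasts, so that both the secondary aim and the usual-care comparison in the Background are covered.
2. Report all other gait, STS and strength variables as exploratory between-arm differences with 95% confidence intervals and no confirmatory significance claims. If strength claims are wanted, state how many scores there are and apply Holm across them; with eight, the smallest p-value is compared with 0.05/8 = 0.00625.
3. Reword the Background hypothesis to refer to the key secondary.
4. Do not make this test conditional on the primary analysis unless success across the three primary scores is defined first.

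The cost is wording, with no new data or participants. The Monitoring section already gives a route for modifications through the ethics committee, and recruitment was still open when the article was published. The small downside is that differences outside the key secondary, and outside any Holm-adjusted strength family, can be reported only as exploratory.
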